#### Missed visits

If a woman is not at home when a scheduled visit was arranged, the support worker calls the woman from the latter’s doorstep. If no response is obtained, a prepared note is left at the woman’s home requesting she contacts the support worker in the next 48 hours. If no contact is made, the support worker contacts the woman. A similar procedure is followed for women who do not attend an appointment scheduled in the community, with follow up letters posted, rather than being left at her home.

### Biological samples taken to assess quitting and gaming

A urine sample is tested at the enrolment visit, using a dipstick test, to assess eligibility for the scheme, with urinary cotinine concentrations equal to or more than 1.5 mg/ml sufficient for enrolment.

Saliva samples are collected by the support worker at 28 weeks gestation, 36 weeks gestation, 2 days post delivery and amongst women reporting cessation, at 6 months post delivery and analysed by a nationally accredited laboratory for cotinine concentrations. For women reporting current use of nicotine replacement therapy, anabasine, a tobacco specific alkaloid, will be analysed.

In addition to being used to biochemically verify quitting, the results of these analyses will be used to estimate the proportions of women reporting having quit who have not. Both women and the support worker will remain blinded to the test results unless a woman requests her result. Women proven to be smoking on any of these extra tests (i.e. those using saliva as opposed to CO) will not be confronted with this, withdrawn from the scheme or refused vouchers. The aim is to estimate the extent of the gaming that is occurring. It is possible for women to abstain for a few hours and pass a CO test but such women would be shown to be smokers by salivary cotinine.

### Post-recruitment retention

Women enrolled in the scheme who do not keep pre-arranged meetings to report their smoking status as per the scheme protocol are contacted by telephone by a support worker. Failure to respond after three attempts at contact is assumed to signal withdrawal from the scheme.

### Data collection and management

Data on women’s progress through the scheme are collected by the support workers and entered onto a data base by a member of the evaluation team. Data on biochemical tests are entered by the evaluation team with the support worker remaining blinded to these results.

### Economic evaluation

No formal economic evaluation is planned for this study. The total budget set aside over two years for the scheme by the Primary Care Trust is £139,000. These costs cover the employment of 1.5 support workers (paid on a pay scale in the range £16,110-£19,077), the costs of the incentives and the laboratory costs for saliva testing. This money does not cover the costs of NHS Stop Smoking Advisors who women access through the existing scheme.

### Precision estimation

This is a single arm intervention study that aims to estimate the proportions of women who join the scheme and who achieve prolonged abstinence, as well as the proportion of women who falsify smoking status to gain rewards. We will offer the scheme for 12 months which will likely involve a group of an estimated 500 pregnant women based upon the number of smokers booking for care at Chesterfield Royal Hospital NHS Foundation Trust in the preceding 12 month period. We estimate that about 30% of smokers approached will enrol, based on 45% recruitment rate in a “cessation induction” trial of incentives that used similar eligibility criteria, conducted in the US [14], and estimated 14% and 10% recruitment rates to two recent UK “aid to cessation” trials for pregnant women trying to quit smoking and not involving any financial incentives [31,32]. A population of 500 will provide an estimate in the region of 30% recruitment with a precision of +/− 4%, using 95% confidence intervals. Estimating 24% quit rates in the 150 enrolled women, based on estimates generated in a recent systematic review [10] will provide an estimate with a precision of +/− 7%, using 95% confidence intervals. We conservatively estimate that the proportion of women quitting will be larger than zero, the rate observed for the preceding period of observation in the study hospital. All women lost to follow-up will be assumed to have resumed to smoking. It is planned to recruit all smokers, regardless of motivation to stop smoking.

### Data analysis

Outcomes will be reported as proportions with 95% confidence intervals for the following: (a) the proportion of pregnant smokers who enrol in the scheme; (b) the proportion of pregnant smokers who participate in the scheme and who achieve prolonged abstinence at i. delivery and ii. six months postpartum; and, (c) the proportion of women who falsely report smoking status to gain entry into the scheme and to gain an incentive. No formal statistical tests will be performed. Rates of prolonged abstinence will be considered to suggest a positive impact of the scheme if the 95% confidence intervals do not include 0%. This is the rate of cessation recorded in a similar population of women in the preceding 12 months in the hospital where the study is taking place.

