### Public attitudes

The use of financial incentives attracts controversy. A recent analysis of media coverage revealed that most articles covered a mix of views [22]. Preliminary results from a series of ongoing experiments reveal that the majority of participants were prepared to trade-off their negative attitudes towards financial incentives against increased effectiveness, i.e. the more effective a scheme, the more acceptable it is judged to be [23].

We describe here a single arm intervention study to be conducted within NHS Derbyshire County at the Chesterfield Royal Hospital NHS Foundation Trust. Between April 2010 to March 2011, 2881 women received care at Chesterfield Royal Hospital NHS Foundation Trust at delivery, out of which a similar proportion smoked at booking (Women smoking at booking n = 500, 17% of total women booking) as they did at delivery (Women smoking at delivery n = 483, 17% of total women delivering). The current study will describe smoking cessation rates in all smokers receiving antenatal care from midwives based at one hospital, Chesterfield Royal Hospital NHS Foundation Trust, for a 12 month period. During this period all pregnant women who smoke will be offered participation in a financial incentive scheme for smoking cessation, regardless of whether they are interested in stopping smoking or planning to use stop smoking services. The current study can therefore be characterized as a “cessation induction” study, as distinct from an “aid to cessation” study, meaning that it aims to encourage women who would not have tried to quit smoking to do so.

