### Study outcomes

#### Smoking cessation: assessed on two occasions

Self-reported, prolonged complete abstinence from smoking (a) between six weeks after enrolment in the scheme and prior to childbirth; and (b) between childbirth and six months later. All women lost to follow-up will be assumed to have resumed smoking. This definition gives women a cessation induction period of up to six weeks, although we expect many women will establish abstinence sooner than this.

These are two outcomes requiring the following different measures:

(a) between six weeks after enrolment in the scheme and prior to childbirth

i. self reported smoking cessation for at least 24 hours at six weeks after enrolment in the scheme, validated by exhaled CO measurement of less than or equal to 6 ppm;

ii. self reported complete abstinence from 6 weeks after enrolment to 36 weeks gestation, validated by salivary cotinine less than 15 ng/ml at 36 weeks. In addition, there must be no reported lapses and a record that all CO readings taken between these dates indicate non-smoking status. All women lost to follow-up will be assumed to have resumed smoking.

(b) between childbirth and six months later

i. self reported smoking cessation for at least 24 hours two days after delivery, validated by exhaled CO measurement of less than or equal to 6 ppm and salivary cotinine less than 15 ng/ml, in keeping with local practice.

ii. self reported complete abstinence from two days after enrolment to six months postpartum, validated by salivary cotinine less than 15 ng/ml at six months. In addition, there must be no reported lapses and a record that all CO readings taken between these dates indicate non-smoking status [27]. All women lost to follow-up will be assumed to have resumed smoking.

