#### Estimating the adverse effects of using incentives to achieve quitting

a) *delay in quitting smoking to enrol in an incentive scheme*: There are concerns that the estimated 11% of women who quit smoking upon learning they are pregnant may delay quitting until they can enrol in the incentive scheme. We will estimate this effect by comparing the self-reported smoking status of women during the time the scheme is running, with that recorded for the preceding 12 months. While this is open to the usual biases associated with historic controls, it will provide some indication of whether the scheme has delayed quitting.

b) *gaming i.e. false reporting of smoking status:* Two types of gaming are possible;

i) *To gain entry to the scheme (i.e. non-smokers acting as smokers).* We will estimate this in two ways: first, using historic controls (by comparing the proportion of women who claim to smoke at the outset of the study with the proportion who reported being smokers in the year prior to the start of the scheme); second, by assessing the proportion of women claiming to smoke with levels of urinary cotinine compatible with non-smoker status. Our inclusion criteria are set to minimise entry to the scheme by non-smokers.

ii) *To gain an incentive (i.e. smokers acting as non-smokers).* We will estimate this by validating CO records and self-reported smoking status against measurement of cotinine collected at 28 weeks gestation, 36 weeks gestation and 2 days after delivery and 6 months post-partum.

The two primary outcomes of this study are:

smoking cessation at delivery; and,

false reporting of smoking status to gain an incentive.

The remaining outcomes will be considered secondary.

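### The 0% reference behind the positive-impact reading has no postpartum basis, yet it is applied to the secondary six-month abstinence rate

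*Protocol article*

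**What the plan says.** The Data analysis section lists the outcomes to be reported as proportions with 95% confidence intervals, among them the women "who achieve prolonged abstinence at i. delivery and ii. six months postpartum". It then says "No formal statistical tests will be performed", and directly afterwards: "Rates of prolonged abstinence will be considered to suggest a positive impact of the scheme if the 95% confidence intervals do not include 0" (0%). The plural subject, coming after a list with two abstinence time points, takes in both. The reason given for 0% is: "This is the rate of cessation recorded in a similar population of women in the preceding 12 months in the hospital". Precision estimation repeats that zero was the rate seen at the hospital in the preceding period.

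The data behind this are in the last paragraph under Public attitudes: 500 women smoking at booking, and "Women smoking at delivery n = 483, 17% of total women delivering". No count is given after delivery.

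On status, the section on adverse effects of incentives introduces its list with "The two primary outcomes of this study are" and names cessation at delivery and false reporting to gain an incentive. It adds: "The remaining outcomes will be considered secondary". Six-month abstinence is therefore secondary.

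Its window is headed "b) between childbirth and six months later" in the smoking cessation outcomes.

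**The concern.** A reference value for an impact reading has to describe what would happen over the same window without the scheme. The protocol's 0% describes the change in smoking between booking and delivery. It is then used, unchanged, for the window from childbirth to six months, for which no hospital figure is shown.

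The two windows differ in substance. Under The incentive scheme, the protocol explains that the schedule restarts after birth partly because women who smoked in pregnancy may then wish to stop. Some women may also stop, or stay stopped, after birth without any scheme. The background section on cessation interventions gives a relapse estimate of 70% in the first six months after delivery. That leaves 30% of quitters abstinent, which is not zero.

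The study aims to inform the use of incentive schemes in routine practice. A statement that the six-month rate suggests a positive impact would carry weight with that audience. Nothing in the document shows that a handful of abstinent women at six months is more than would occur anyway.

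**Working it through.** **Inputs.** Expected enrolment is 30% of 500 = 150 women, and the expected quit rate is 24% (Precision estimation). Smokers number 500 at booking and 483 at delivery (Public attitudes). Postpartum relapse is 70% (Smoking cessation interventions in pregnant women). The type of confidence interval is not stated, so three common ones are used.

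**1. The plan's own precision figures.** Half-width = 1.96 × √(p(1 − p)/n).
- 30% of 500: 1.96 × √(0.30 × 0.70/500) = 4.02 points; stated as 4.
- 24% of 150: 1.96 × √(0.24 × 0.76/150) = 6.83 points; stated as 7.

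Both reproduce. They do not reveal the interval type: at 36 of 150 the Wilson interval (17.9% to 31.4%) and the exact interval (17.4% to 31.6%) also have half-widths that round to 7.

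**2. How many abstinent women of 150 put the lower limit above 0%?**
- Exact (Clopper-Pearson), 1 woman: lower limit 1 − 0.975^(1/150) = 0.02%, upper 3.66%. One is enough.
- Wilson, 1 woman: 0.12% to 3.68%. One is enough.
- Normal limits, 3 women: 2.00% − 1.96 × √(0.02 × 0.98/150) = 2.00% − 2.24%, below zero. With 4 women: 2.67% − 2.58% = 0.09%. Four are needed.

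**3. Chance of meeting the rule when the scheme has no effect.** This needs the background six-month rate in comparable women, which the document does not give. The rates below are assumptions. With X binomial (150, p), P(X ≥ 1) = 1 − (1 − p)^150, and P(X ≥ 4) is the upper binomial tail.

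| Assumed background rate | 1 woman suffices | 4 women needed |
|---|---|---|
| 0% | 0 | 0 |
| 1% | 78% | 6% |
| 2% | 95% | 35% |
| 3.4% | 99.4% | 75% |

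For orientation only: the hospital's net fall is (500 − 483)/500 = 3.4%. If 30% of such women stayed abstinent, the six-month rate would be 0.034 × 0.30 = 1.0%. This treats a net change in prevalence as a quit rate and leaves out women who stop after birth. It is not an estimate of the missing comparator; it shows only that rates of this order are not far-fetched.

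**4. Chance of meeting the rule under the plan's expectations.** If 24% quit and 70% of them relapse, 0.24 × 0.30 = 7.2% remain abstinent at six months. P(X ≥ 4) is then 99.5%, and P(X ≥ 1) is above 99.9%. The positive reading at six months is close to certain before the data are seen.

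**5. Can the six-month outcome be met without the delivery outcome?** The heading of outcome (b) and the rationale for restarting the schedule after birth say yes. Criterion (b)ii, however, starts the abstinence period two days after enrolment, which taken literally reaches back into pregnancy. The surrounding text suggests a slip, but the passages conflict and need reconciling. The missing postpartum comparator does not depend on how that is settled.

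**The case against.** The strongest reply is that this is an estimation study. It disclaims formal tests, sets no alpha or power, plans on precision, says only that a rate would suggest an impact, and concedes in the Discussion that it has no comparison group. All of that stands.

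It disposes of a stronger reading that a reader might infer: that one rule over two rates, without an order between them, inflates the chance of a false claim, so that success could be declared on the secondary outcome alone. The document does not support this, for four reasons.
- It never says that either rate suffices for an overall conclusion. Each rate may speak for its own time point, or both may be required.
- If the true rate really is 0%, the chance of meeting the rule is exactly zero for one rate or for both, so there is no error for a hierarchy to control.
- The probabilities in the working come from the 0% reference, not from having two outcomes.
- At the planned 24% of 150, the delivery rate meets the rule with probability above 0.9999, so a conflict between the two rates is remote unless true quit rates are around 1% to 3%.

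It would also go too far to say that no postpartum rate exists. None is shown, and this is a condensed article.

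What the reply does not answer is the sentence itself. Having disclaimed tests, the plan still fixes a threshold for reading the six-month rate as a positive impact and states a source for it. The counts shown from that source stop at delivery. The Discussion's general caveat does not withdraw the six-month reading.

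**Conclusion.** The point holds in a limited form. The impact reading at six months rests on a reference value for which the document shows no postpartum basis, and it is attached to a secondary outcome. As written, one to four abstinent women of 150 would trigger it, depending on the interval. At an assumed 2% background rate it would be triggered with probability 95% (exact or Wilson) or 35% (normal limits) with no effect of the scheme; at 1% the figures are 78% and 6%.

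These figures assume that all 150 expected women are in the denominator; the planned exclusions for death, untraceable address, miscarriage and stillbirth would change it slightly. The background rates are assumptions, and the interval type is unstated.

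No multiplicity or error-rate defect is claimed. Whether 0% is right at delivery is a separate question. The change is worth making because it removes an unsupported conclusion at little cost.

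**What to change.** In Data analysis, restrict the impact sentence to the rate of prolonged abstinence at delivery. Add a sentence along these lines: *Abstinence from childbirth to six months is a secondary outcome; it will be reported as a proportion with its 95% confidence interval and will not be interpreted as evidence of impact, because no comparator for that period is available.* If an impact reading at six months is wanted, state a postpartum comparator with its source and population, and judge the interval against that value instead of 0%.

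Reconcile the start of the abstinence period in criterion (b)ii with the heading of outcome (b), so that it is clear which women can count.

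The cost is one or two sentences, with no change to sample size, data collection or procedures. The downside is that a favourable six-month rate becomes descriptive.

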## Study aim and objectives

The aim of this study is to assess the potential effectiveness of using financial incentives to achieve smoking cessation in pregnant women who smoke, to inform the use of financial incentive schemes in routine clinical practice as well as the interpretation of existing trials and the design of future studies.

The specific objectives of the study are:

1) To estimate the proportion of pregnant women who smoke at the point of receiving antenatal care from midwives, at one hospital over a 12 month period, who accept the offer to participate in a financial incentive scheme for smoking cessation

2) To estimate the proportion of pregnant women who smoke, and who participate in the scheme and achieve prolonged abstinence at (a) delivery and (b) six months post-partum

3) To examine predictors of (a) participation in the scheme, and (b) smoking cessation

4) To estimate the prevalence of two possible sets of adverse effects of using incentives to achieve quitting:

a) Delay in quitting, in order to enrol in an incentive scheme

b) Gaming *i.e.* false reporting of smoking status:

i) to gain entry to the scheme (i.e. non-smokers acting as smokers)

ii) to gain an incentive (i.e. smokers acting as non-smokers)

5) To describe the process of visits for incentive payment assessments both in patients’ homes and in clinic settings. This will include the total number of visits, the length of each visit, visits defaulted, mileage travelled and total time taken.

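### The impact rule sets a quit rate in about 150 self-selected, cotinine-screened women against a historical rate from all booked smokers, so it does not compare like with like

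*Protocol article*

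**What the plan says.** The rule is in the protocol article, Data analysis: "Rates of prolonged abstinence will be considered to suggest a positive impact of the scheme if the 95% confidence intervals do not include 0" (0%). The reason given for 0% is "This is the rate of cessation recorded in a similar population of women in the preceding 12 months" at the same hospital. Precision estimation repeats the benchmark, expecting a proportion of quitters "larger than zero, the rate observed for the preceding period of observation in the study hospital".

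The quit rate to be judged is sized in Precision estimation: "Estimating 24% quit rates in the 150 enrolled women". The 150 comes from "We estimate that about 30% of smokers approached will enrol", applied to about 500 smokers.

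The only historical counts in the article are under Public attitudes, and they cover every smoker booked: "Women smoking at booking n = 500, 17% of total women booking" and "Women smoking at delivery n = 483, 17% of total women delivering".

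The wording on the denominator is not uniform. Objective 2 reads "To estimate the proportion of pregnant women who smoke, and who participate in the scheme and achieve prolonged abstinence", which could mean a proportion of all pregnant smokers. Precision estimation uses enrolled women. So does the rule under Exclusion criteria that counts women who drop out of the scheme as smokers.

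**The concern.** Enrolled women differ from all booked smokers in two ways that the protocol itself describes. Under Enrolment, they are women who ask to be considered. Under Recruitment and screening, they must also reach a urinary cotinine threshold, and the scheme is presented to them as meant for heavier smokers. Standard stop smoking support is offered whether or not a woman joins, so some quitting can occur without any incentive effect.

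If women who would have stopped anyway are more likely to enrol, the enrolled quit rate exceeds the all-smoker rate even when the scheme does nothing. This is separate from the value of the benchmark: it remains when 0% is replaced by another all-smoker rate.

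Smoking cessation at delivery is one of the two primary outcomes, and the stated aim is to inform routine practice. The article also presents the study as one meant to prompt quitting among women who would not otherwise have tried, with the offer made to every smoker. The matching denominator for a claim of impact is therefore all booked smokers.

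**Working it through.** **Inputs**
- Smokers in the preceding year: 500 at booking, 483 at delivery (Public attitudes).
- Expected uptake 30% of 500 = 150; assumed quit rate 24%, so 0.24 × 150 = 36 quitters (Precision estimation).
- Decision rule: the 95% interval excludes 0% (Data analysis).
- Assumption, not in the protocol: an enrichment factor k, the background quit rate among enrollers divided by that among all booked smokers. Its maximum is 500/150 = 3.33, when every background quitter enrols.

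**Step 1: the plan's own precision.** Half-width = 1.96 × √(p(1 − p)/n).
- Uptake: 1.96 × √(0.30 × 0.70/500) = 4.0 points (stated ±4%).
- Quit rate: 1.96 × √(0.24 × 0.76/150) = 6.8 points (stated ±7%).

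Both reproduce. The second confirms that the quit rate was planned on 150.

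**Step 2: the background rate.** 500 − 483 = 17, and 17/500 = 3.4% (exact 95% CI 2.0–5.4%). This is a net change in recorded status, not 17 identified quitters; it may hide quitting offset by relapse.

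**Step 3: the planned 0% rule under no effect.** With n = 150, the interval excludes 0% from 4 quitters upward (Wald) or from 1 (exact). At a 3.4% background and no enrichment, the rule is met with probability 75% (Wald) or 99% (exact). Changing only the denominator does not help: 17/500 also has an interval (2.0–5.4%) that excludes 0%.

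**Step 4: isolating self-selection.** Replace 0% by 3.4% and use exact intervals.
- On 150, the lower limit exceeds 3.4% from 11 quitters upward. The no-effect chance is P(X ≥ 11), X ~ Binomial(150, 0.034k).
- On 500, it exceeds 3.4% from 26 upward. The chance is P(X ≥ 26), X ~ Binomial(500, 0.034).

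| Denominator | k | Chance of a false positive |
|---|---|---|
| 150 enrolled | 1 | 1.4% |
| 150 enrolled | 1.5 | about 15% |
| 150 enrolled | 2 | 44% |
| 150 enrolled | 3 | 91% |
| 150 enrolled | 3.33 | 96% |
| 500 booked | not applicable | 2.3% |

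At the extreme, 17/150 = 11.3% (6.7–17.5%).

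**Step 5: the planning figures on each denominator.** 36/150 = 24.0% (17.4–31.7%); 36/500 = 7.2% (5.1–9.8%). Set against 17/500, the difference is 7.2 − 3.4 = 3.8 points (Newcombe 95% CI 1.0 to 6.7). This last figure only illustrates scale, because it mixes verified quitters with a net recorded change.

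**The case against.** **The benchmark is the larger fault.** A reader might infer that self-selection alone yields a positive result, or that moving to 500 repairs the rule. The documents support neither. If the background rate were truly 0%, no subset could show quitting without an effect. At 3.4%, the 0% rule is usually met with no enrichment at all, and on 500 as well as on 150. This stands. It means that both the benchmark and the denominator must change.

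**Enrichment is assumed.** A reader might take the 96% as the expected error. It is the extreme at which all background quitters enrol, and nothing in the protocol says that this will happen. The cotinine threshold may select women who find quitting harder. The outcome is also stricter than recorded status: under Study outcomes it needs negative CO readings throughout and salivary cotinine below 15 ng/ml, with losses counted as smokers. Both may offset enrichment to an unknown degree. They are also further ways in which the two rates are unlike.

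**The claim is already modest.** The plan disclaims formal tests and speaks only of suggesting an impact, and the Discussion admits that there is no untreated comparison group. That softens the inference. The Discussion does not name self-selection or the mismatched denominators, however, and the check against 0% remains the stated criterion.

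**The denominator may be all smokers.** Objective 2 allows that reading, but the stated precision of ±7% then belongs to a different quantity. A correction is needed either way.

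**The alternative is also biased.** Routine records in the scheme year are open to the false reporting described under Unintended perverse effects of incentive schemes and under the adverse-effect estimates. This stands and must be stated with the result.

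**Conclusion.** The concern holds in a limited form. The protocol's claim of a similar population is not supported by its own recruitment process, and the two rates also measure different things: validated prolonged abstinence against net recorded smoking status. Given any non-zero background rate, self-selection can raise the enrolled rate above the all-smoker rate with no effect of the scheme.

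With the benchmark at 3.4%, twofold enrichment is enough to turn a 1.4% false-positive chance into 44%. These figures rest on the net 17/500 as the background rate, exact intervals, and an assumed enrichment between 1 and 3.33 times. They show what the rule allows; they do not predict that enrichment will occur or how large it will be.

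**What to change.** In Data analysis:
1. State that the quit rate in enrolled women (about 150) is descriptive, and drop its comparison with the previous year.
2. Base any statement about impact on all women recorded as smoking at booking in the scheme year (about 500). Compare them with the preceding year on the same routinely recorded definition, with a 95% confidence interval for the difference between years in place of the check against 0%.
3. Report cotinine-verified quitters over all booked smokers beside it.
4. Say that the comparison remains historical, and that false reporting of smoking status in the scheme year could inflate it.

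Precision estimation should drop the 0% benchmark and name the denominator of each proportion.

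The cost is some rewording and one further proportion, using the kind of hospital counts already given under Public attitudes. The downside is a less favourable headline, about 7% instead of 24% at the planning figures.
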